### Sample Size

Results from G^∗^Power calculations for repeated measures analysis, assuming a *p*-value = 0.05, an effect size of *f* = 0.25 (Scott et al., 2018), with a statistical power of 0.95, three groups, and four measurements, recommend a sample size of 171. Giving the 30% drop-out rate in previous ACT-based intervention studies (Melville et al., 2010), the total sample size to be collected will be 246 (each group will be composed of 82 participants).

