### Statistical Analysis

The efficacy of the iACTwithPain will be assessed by comparing pre-intervention, post-intervention, and 3- and 6-month follow-up questionnaires’ scores through MANOVAs, repeated measures, within-between interaction (with Bonferroni correction). Changes in the primary outcome and in the secondary outcomes between pre-intervention, post-intervention, and follow-ups will be compared between the three conditions (iACT, iACTwithPain, and waiting-list). MANOVAs’ assumptions (multivariate normality, linearity, absence of multicollinearity, and equality of covariance matrices) will be analyzed prior to analysis.

Additionally, changes in painkillers dependence and hospital visits (self-disclosed) will also be compared between the three groups. Cohen’s *d* will be calculated to measure the between-group effect size on both primary and secondary outcomes. Changes in psychological processes (e.g., self-compassion, mindfulness, and psychological flexibility) will also be tested as potential mechanisms of change of the iACTwithPain intervention, using mediation modeling procedures. Missing data will be imputed with PASW Missing Value Analysis (SPSS Inc., United States) (Blankers et al., 2010).

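### Missing scores are to be imputed and then tested by repeated-measures MANOVA with no stated step that carries imputation uncertainty, so the wording permits a test on one completed data set at 30% drop-out

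*Protocol article*

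**What the plan says.** Three sections of the protocol article bear on this point.

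- **Sample Size.** The calculation is "assuming a *p*-value = 0.05, an effect size of *f* = 0.25", "with a statistical power of 0.95, three groups, and four measurements, recommend a sample size of 171". It is then raised for attrition: "Giving the 30% drop-out rate in previous ACT-based intervention studies (Melville et al., 2010), the total sample size to be collected will be 246", in three groups of 82.
- **Statistical Analysis.** T0 to T3 scores are compared "through MANOVAs, repeated measures, within-between interaction (with Bonferroni correction"). The section ends its account of missing data with "Missing data will be imputed with PASW Missing Value Analysis (SPSS Inc., United States"), followed by a literature citation. It does not say whether imputation is single or multiple, whether arm is in the imputation model, or how results are combined.
- **Implementation of the Interventions.** Participants who skip more than two sessions are not considered for the RCT, and iACTwithPain participants who do not complete both compassion sessions are also excluded. The control arm has no sessions, so neither rule can reach it.

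**The concern.** The stated level and power describe a test on about 172 people with four observed scores each. If missing scores are filled in once and the MANOVA is run on the completed file, the test treats up to 246 people as fully observed, and about 74 of them contribute values made from the others. What follows depends on the imputation model.

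- **Arm included.** The error variance is too small and the error degrees of freedom too large, so the test rejects too often.
- **Arm omitted.** Drop-outs from all arms are filled in from one common regression. The arm difference, and the Cohen's *d* that the plan will report, are pulled toward zero.

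Either would affect the main efficacy result. Drop-out is not a remote case either, since the Discussion calls its prevention one of the trial's most significant challenges.

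**Working it through.** **1. The plan's own figures.** Inputs from Sample Size: k = 3 groups, m = 4 measurements, f = 0.25, level 0.05, power 0.95. For the Pillai within-between interaction test:

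- s = min(k − 1, m − 1) = 2
- df1 = (k − 1)(m − 1) = 6
- λ = N·s·f² = 171 × 2 × 0.0625 = 21.4
- df2 = s(N − k − (m − 1) + s) = 2 × (171 − 3 − 3 + 2) = 334

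Power is 0.9499 at N = 170 and 0.9512 at N = 171, so 171 reproduces exactly. For drop-out, 171 / 0.70 = 244.3, which rounds up to 245 and then to 246 for three equal arms. In return, 246 × 0.70 = 172.2, with power 0.953 at 172. The number expected to be lost is 246 − 172 = 74. If all 246 were counted as observed, the same formula would read 0.994, which overstates the information in the data.

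**2. Why a single completed file misleads: a hand check.** Suppose 30% are lost after T0 and filled in with conditional means by arm. Consider the part of a follow-up score that T0 does not predict, with variance σ². The arm mean really rests on 82 × 0.70 = 57.4 people, so its variance is σ²/57.4. The MANOVA sees a within-arm variance of 0.70σ² and divides by 82. The ratio of apparent to true variance is 0.70 × 57.4 / 82 = 0.49. On 6 degrees of freedom the 5% chi-square point of 12.59 then acts like 12.59 × 0.49 = 6.17. With x = 6.17/2 = 3.085, the tail probability is e^(−x)(1 + x + x²/2) = 0.0457 × 8.84 = 0.40. The simulated figures should fall somewhat below this, because T0 itself is fully observed.

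**3. Simulated false-positive rate at nominal 0.05.** Assumptions, none of them given in the article: multivariate normal scores, equal correlation 0.5 or 0.7 between visits, and 30% missing completely at random. Drop-out is either all after T0 or a further 10% at each of T1 to T3. There were 82 per arm, Pillai's test and 4,000 replicates. Cells show correlation 0.5 / 0.7.

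| Handling | All lost after T0 | Spread over T1–T3 |
|---|---|---|
| Full data | 0.051 / 0.045 | 0.050 / 0.052 |
| Complete cases | 0.048 / 0.052 | 0.043 / 0.049 |
| Single, arm in model, conditional mean | 0.344 / 0.376 | 0.221 / 0.236 |
| Single, arm in model, one random draw | 0.261 / 0.281 | 0.187 / 0.191 |
| Single, arm omitted, conditional mean | 0.051 / 0.047 | 0.051 / 0.051 |

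Separate runs under the same assumptions put single imputation with arm at about 0.16 to 0.38 overall. One run of 3,000 replicates gave 0.39, which is within simulation error.

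**4. The exclusion rule applied.** Assume that active-arm participants lost after T0 are removed under the session-skipping rule and only the remaining gaps are imputed, with arm in the model. With all loss after T0, conditional-mean imputation gives 0.13 / 0.14 and one random draw 0.11 / 0.11. With spread loss the figures are 0.17 / 0.18 and 0.14 / 0.15. Across runs the range is about 0.10 to 0.18.

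**5. Size of the effect.** Take a true difference of 0.50 SD. With arm omitted and all loss after T0, drop-outs contribute no arm difference, so the expected estimate is 0.70 × 0.50 = 0.35. The simulation gives 0.349. With spread loss, only 10% are missing at T1, so the expected T1 estimate is 0.90 × 0.50 = 0.45. At T3 the simulation gives 0.401. Across runs the estimates lie between 0.34 and 0.46, a shrinkage of roughly 10% to 30%. Complete cases and single imputation with arm both give 0.495 to 0.503.

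**6. Pooled multiple imputation with arm.** With 40 imputations and correlation 0.5, the false-positive rate is 0.054 and 0.058 for the two drop-out patterns. The same Wald-type test on full data gives 0.058 and 0.061. With fewer imputations and 1,000 replicates the rates were 0.055 to 0.075. Pooled estimates of the 0.50 SD difference were 0.486 to 0.512.

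**The case against.** The strongest reply is that the article never says single imputation. It says scores will be imputed, names a module and cites a source that is not available here. The number of imputations, the model and the pooling are details that a condensed article may leave to a plan not shown. This stands against one stronger reading: a reader might infer that the 0.05 level or the effect estimate fails under this plan. The text does not support that, because pooled multiple imputation including arm would keep both in these scenarios.

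A reader might also infer that the sample size contradicts the analysis, since it counts 30% as lost and the analysis then fills them in. That is not supported either. Recruiting 246 protects the information available, imputing afterwards does not conflict with it, and the article does not claim that imputed people add to N.

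A third reply is that error rates of 34% to 38% assume every early drop-out in every arm is imputed, whereas the exclusion rule would remove many of those in the active arms. This too stands. It brings the rate down to about 0.10 to 0.18, which is still two to three and a half times nominal.

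What does not stand is that only a missing detail is at issue. The article does fix a strategy, imputation followed by MANOVA. The named test is an omnibus multivariate F, whereas Rubin's rules combine estimates and their variances. Imputing and then running the MANOVA does not by itself produce a valid pooled test.

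**Conclusion.** The concern holds in a limited form. The plan commits to imputation followed by MANOVA without a method that carries imputation uncertainty, at an expected 30% drop-out. The wording permits an analysis with a false-positive rate of about 0.16 to 0.38 (about 0.10 to 0.18 with the active-arm exclusions), or, with arm omitted, an effect shrunk by roughly 10% to 30%. Which of these occurs, or whether neither does, depends on a choice the text leaves open.

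The sizes rest on the assumed correlations, normality, drop-out patterns and missingness completely at random. Informative drop-out was not simulated and could bias any of these analyses. The figures of 171 and 246 are correct.

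**What to change.** Replace the imputation sentence with one of two methods:

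- a likelihood-based repeated-measures model on all observed PIQ-6 scores, with arm, time and arm-by-time terms and an unstructured covariance; or
- multiple imputation that includes arm and all time points, with the arm contrasts pooled by Rubin's rules.

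State that a MANOVA on one completed data set will not be used. Say whether participants who meet the session-skipping or compassion-session exclusion are removed or kept with their missing scores handled by the chosen method, and reconcile this with the fact that the rule can apply only to the active arms.

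The cost is some rewording, some extra analysis work, and intervals that are wider, and correct, compared with those from a single completed file. No new data or participants are needed, and the Sample Size section need not change.

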## Discussion

To our current knowledge, iACTwithPain will be the first eHealth intervention that incorporates ACT and explicit self-compassion elements. This intervention is expected to improve CP patients’ psychosocial functioning and quality of life, by promoting adaptive disease management and regulation of pain-related internal experiences. By providing access to specialized treatment with an online delivery format and self-management nature, the intervention is also expected to promote patients’ empowerment and accessibility to treatment. Results will contribute to better understand self-compassion’s individual role in ACT for CP, the pertinence of adding compassion-promoting exercises to those interventions, and to reach an optimized intervention for this population.

One of this study’s strengths is the analysis of the potential mechanisms of change of the tested interventions, which will shed light on which therapeutic processes are responsible for improvements in CP, in both the iACTwithPain intervention and the ACT-only intervention. Another strength is the platform itself, which will be developed aiming at being intuitive and graphically attractive and which will track participants’ interaction, providing objective data on participants’ between-session practice and engagement with the interventions, which will be examined and accounted for in the efficacy test.

One of the most significant challenges will be the prevention of drop-outs. A strategic way of decreasing this risk will be to email participants with supportive and motivating messages every time the platform registers inactivity for more than 3 days. Another limitation will be that participants allocated to the control group (medical TAU) will not be blind to their allocation due to the nature of this condition, which might influence self-reported outcomes.

In conclusion, this study will contribute with a new eHealth self-management intervention for CP, which, if proven effective, will significantly help CP patients manage their pain and improve their mental health and quality of life and improve accessibility to treatment of remote clinical cohorts or with limited mobility. With this RCT, specific knowledge will be obtained about the role of self-compassion in ACT for CP and the potential benefits of adding explicit self-compassion elements to ACT.

## Ethics Statement

The studies involving human participants were reviewed and approved by Comité de Ética e Deontologia (CEDI), Faculty of Psychology and Education Sciences, University of Coimbra. The patients/participants provided their written informed consent to participate in this study. Written informed consent was obtained from the individual(s) for the publication of any potentially identifiable images or data included in this article.
